## Abstract

**Background:**

Brain injuries resulting from motor vehicle accidents and falls, as well as hypoxic insults and other conditions, are one of the leading causes of disability and death in the world. Current treatments are limited but include continuous rehabilitation, especially for chronic brain injury. Recent studies have demonstrated that the intravenous infusion of mesenchymal stem cells (MSCs) has therapeutic efficacy for several neurological diseases, including stroke and spinal cord injury.

**Objective:**

The objective of our investigator-initiated clinical trial is to assess the safety and potential efficacy of the intravenous infusion of autoserum-expanded autologous MSCs for patients with chronic brain injury.

**Methods:**

The (phase 2) trial will be a single-arm, open-label trial with the primary objective of confirming the safety and efficacy of autoserum-expanded autologous MSCs (STR-01; produced under good manufacturing practices) when administered to patients with chronic brain injury. The estimated number of enrolled participants is 6 to 20 patients with a modified Rankin Scale grade of 3 to 5. The assessment of safety and the proportion of cases in which the modified Rankin Scale grade improves by 1 point or more at 180 days after the injection of STR-01 will be performed after MSC infusion.

**Results:**

We received approval for our clinical trial from the Japanese Pharmaceuticals and Medical Devices Agency on December 12, 2017. The trial will be completed on June 11, 2023. The registration term is 5 years. The recruitment of the patients for this trial started on April 20, 2018, at Sapporo Medical University Hospital in Japan.

**Conclusions:**

Our phase 2 study will aim to address the safety and efficacy of the intravenous infusion of MSCs for patients with chronic brain injury. The use of STR-01 has been performed for patients with cerebral infarction and spinal cord injury, providing encouraging results. The potential therapeutic efficacy of the systemic administration of autoserum-expanded autologous MSCs for chronic brain injury should be evaluated, given its safety and promising results for stroke and spinal cord injury.

**Trial Registration:**

Japan Medical Association Center for Clinical Trials JMA-IIA00333; https://tinyurl.com/nzkdfnbc

**International Registered Report Identifier (IRRID):**

DERR1-10.2196/37898

## Introduction

### Background

A *brain injury* is defined as an alteration in brain function or other evidence of brain pathology caused by trauma, including trauma resulting from motor vehicle accidents, falls, hypoxic insults, infections, and other conditions. Survivors—not only in severe cases but also in moderate or mild brain injury cases—experience the significant burdens of physical and neuropsychological disabilities. These disabilities disrupt the lives of patients and their families and result in substantial health care and social costs [1]. Chronic histopathological changes, such as cell death, axonal injury, vascular damage, and inflammation, have long-term persistence in brain injury survivors [2]. Thus, it is important to develop a novel approach to treating chronic brain injury.

The intravenous infusion of mesenchymal stem cells (MSCs) has shown therapeutic efficacy in experimental animal models of neurological diseases and injuries, including cerebral ischemia [3-12], spinal cord injury (SCI) [13-16], chronic epilepsy [17], and peripheral nerve injury [18-20]. The suggested therapeutic mechanisms of MSCs from animal studies include the secretion of neurotrophic factors that can provide neuroprotection [14,17,21], neovascularization [22,23], the restoration of the blood-brain barrier [13,24], the regeneration of axonal injury [13,25], remyelination [13], synaptogenesis [12,25], induced neural plasticity [12,25], and remote effects [15]. These therapeutic mechanisms may have beneficial effects on chronic brain injury as well. We also conducted clinical studies in which the intravenous infusion of autologous MSCs in patients with stroke [26,27] and SCI [28] was performed, and we showed its safety and improvements in neurologic symptoms. Thus, we hypothesize that the intravenous infusion of MSCs may have therapeutic efficacy for patients with chronic brain injury.

### Objectives

The objectives of the proposed clinical trial include evaluating the safety and efficacy of intravenously infused autologous MSCs that are expanded with autosera in patients with chronic brain injury.

## Methods

### Study Design

The (phase 2) trial will be a single-arm, open-label trial. The outline of the clinical protocol is shown in Figure 1. We will infuse the MSCs at least 180 days after onset. This trial will be carried out at Sapporo Medical University Hospital, Japan. The study protocol was based on advice provided by the Pharmaceuticals and Medical Devices Agency (PMDA) in Japan.

**Figure 1 figure1:**
[figure not shown]
Clinical protocol. FMA: Fugl-Meyer assessment; MSC: mesenchymal stem cell.

We propose to provide an extensive rehabilitation protocol to all participants prior to MSC infusion in order to exclude the potential effects of rehabilitation alone and evaluate MSC-specific effects. Briefly, all patients with chronic brain injury will receive formal rehabilitation (at least 80 min/weekday for 4 weeks) and continue formal rehabilitation until they show no further improvements in Fugl-Meyer assessment (FMA) scores for the last 2 weeks prior to MSC infusion. Thus, we expect to evaluate the therapeutic effects of MSC infusion in addition to the effects of rehabilitation therapy. We will evaluate FMA scores approximately every week. The clinical data will be collected by at least 1 physical therapist and at least 1 Japanese board-certified neurosurgeon at Sapporo Medical University Hospital. If the patients require more than 2 weeks to reach an FMA score plateau, we will continue formal rehabilitation until they show no further improvements for the next 2 weeks.

For cell preparation, peripheral blood draws from each patient for autoserum and bone marrow collection will be performed. The autologous MSCs will be cultured in autologous sera, and the autologous human MSCs (called *STR-01*) will be manufactured in a cell processing center at Sapporo Medical University. STR-01 will be prepared under good manufacturing practice conditions by personnel, who have received formal good manufacturing practice training, within a facility with highly controlled temperature, room air, pressure, and environmental conditions and then cryopreserved at −150 °C until its use, as previously described [28]. On the day of infusion, cryopreserved units will be thawed at the bedside in a 37 °C water bath and will be administered with saline to each patient for approximately 60 minutes. The total number of cells in the STR-01 product is based on our previous study (0.5 × 10^8^ to 2 × 10^8^ cells per patient) [27]. Hospital treatment, including rehabilitation for a target of 80 min/weekday, will be performed for 180 (±14) post-MSC infusion days, after which final outcome measures will be evaluated.

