
### Inclusion Criteria at the Time of the Second Registration

For the second registration, the inclusion criteria will be as follows: (1) ≥180 days after the onset of a brain injury other than stroke; (2) patients who, after rehabilitation for at least 80 minutes per weekday or as much as possible over the past 1 month or more, showed no improvement in FMA score over the last 2 weeks (definition of *improvement in FMA score*: improvement by 1 point or more, as shown by the total FMA score); (3) a classification of grade 3 to 5 on the mRS; and (4) patients who are ready for the infusion of STR-01 that satisfies the specifications of the acceptance criteria.

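### The pre-infusion rehabilitation run-in cannot exclude rehabilitation effects in a single-arm trial that continues rehabilitation for 180 days, and its required intensity is stated inconsistently

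*Protocol article*

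**What the plan says.** All places are in the protocol article.

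- **Design** (Study Design): "The (phase 2) trial will be a single-arm, open-label trial".
- **Purpose of the run-in** (Study Design, text after Figure 1): rehabilitation precedes infusion "in order to exclude the potential effects of rehabilitation alone and evaluate MSC-specific effects".
- **Content of the run-in** (same text): all patients receive formal rehabilitation of "at least 80 min/weekday for 4 weeks" and then "continue formal rehabilitation until they show no further improvements in Fugl-Meyer assessment (FMA) scores for the last 2 weeks prior to MSC infusion". On monitoring: "We will evaluate FMA scores approximately every week".
- **After infusion** (same text): "Hospital treatment, including rehabilitation for a target of 80 min/weekday, will be performed for 180 (±14) post-MSC infusion days", and the final outcomes are read after that.
- **First registration, inclusion criterion 4**: rehabilitation of at least 80 minutes per weekday must be feasible, with no exception.
- **Second registration, inclusion criterion 2**: the patient must show no gain of 1 point or more in total Fugl-Meyer assessment (FMA) score over the last 2 weeks, "after rehabilitation for at least 80 minutes per weekday or as much as possible over the past 1 month or more".
- **Primary Outcome**: the proportion of patients whose mRS grade improves by at least 1 point from just before infusion to day 180 (±14).
- **Statistical Analysis, Primary Outcome Measure**: a Z-test with continuity correction, taking the improvement rate without cells to be 0.1%.

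**The concern.** The run-in is given a property that the design does not have. Bringing patients to a plateau before baseline can reduce the contribution of rehabilitation. It cannot remove it when about 26 further weeks of rehabilitation follow and no concurrent group receives that rehabilitation without cells. The plateau is also judged over 2 weeks on FMA, whereas the outcome is mRS half a year later. A change in mRS after baseline is therefore the joint result of cells, continued rehabilitation and time.

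This reaches the primary test. A null rate of 0.1% is tenable only if rehabilitation and time contribute almost nothing after baseline, which is what the run-in is said to guarantee. If the guarantee fails, a significant result does not point to the cells.

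A second, separate matter is the intensity of the run-in. The Study Design text sets an unconditional floor, and the criterion that admits patients to infusion does not.

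**Working it through.** The plan gives no figure for this point, so there is none to reproduce.

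**1. Amount of rehabilitation before and after baseline**

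Inputs from the Study Design text: 80 min/weekday in both periods, a minimum run-in of 4 weeks, and follow-up of 180 (±14) days. The calculation takes 5 weekdays per week and full delivery of the post-infusion target.

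- Minimum run-in: 4 × 5 × 80 = 1,600 min = 26.7 h.
- After infusion: 180/7 = 25.7 weeks; 25.7 × 5 × 80 = 10,286 min = 171.4 h.
- Ratio: 10,286/1,600 = 6.4. At 166 days it is 5.9 and at 194 days 6.9.

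The minutes per weekday cancel, so this is simply 25.7 weeks over 4 weeks. The run-in is open-ended, so the ratio is not fixed. For assumed run-ins of 6, 8 and 12 weeks it is 4.3, 3.2 and 2.1 at 180 days.

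**2. What the primary test needs in order to be positive**

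Inputs: p0 = 0.001 (Primary Outcome Measure) and n = 6, 10 and 20, the sizes named under Sample Size. With r improvers,

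z = (r/n − p0 − 1/(2n)) / √(p0(1 − p0)/n).

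For r = 1:

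- n = 6: (0.1667 − 0.001 − 0.0833)/0.01290 = 6.4
- n = 10: (0.1 − 0.001 − 0.05)/0.00999 = 4.9
- n = 20: (0.05 − 0.001 − 0.025)/0.00707 = 3.4

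The article states neither alpha nor sidedness. All three values exceed 1.96, the two-sided 5% limit. One improver is therefore enough at each size.

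**3. Chance of a positive result if the cells do nothing**

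Let q be the proportion improving by at least 1 mRS grade through rehabilitation and time alone. The chance of at least one improver is 1 − (1 − q)^n.

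| q | n = 6 | n = 10 | n = 20 |
|---|---|---|---|
| 0.1% (plan's assumption) | 0.6% | 1.0% | 2.0% |
| 1% (assumed) | 5.9% | 9.6% | 18.2% |
| 5% (assumed) | 26% | 40% | 64% |

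**4. The run-in wordings side by side**

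- Study Design: at least 80 min/weekday for 4 weeks, for all patients.
- First registration: 80 min/weekday must be feasible.
- Second registration: 80 min/weekday, or whatever could be managed, over 1 month or more.

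A patient can satisfy the third wording while breaching the first. That patient would reach the plateau on a lighter programme and then be treated toward the 80-minute target.

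**The case against.** A plateau design does not need equal cumulative hours. It relies on there being no further gain at a given intensity, and the nominal intensity is the same before and after infusion. The article also softens its claim. Shortly after the sentence quoted, it speaks of assessing the cells' effect over and above that of rehabilitation. Elsewhere it speaks of potential efficacy and of a later controlled, blinded study. A single arm is openly declared and is an ordinary choice in phase 2.

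Much of this stands. The 6.4 describes duration only, the single arm is not itself a fault, and the remedy is largely one of wording. But the softer sentence does not withdraw the claim of exclusion, and a single arm cannot separate the two effects under either sentence. Two flat weeks on FMA are also thin support for a near-zero mRS improvement rate over the next 26 weeks.

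Three stronger readings are tempting and are not supported:

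- **That intensity rises after baseline and so favours the product.** The second-registration wording permits a rise, but none is planned. The post-infusion figure is only a target, and a patient who fell short before infusion may fall short after it.
- **That the plateau rule passes a known share of patients who are still improving.** The documents give no FMA measurement error. With an assumed error SD of 2 points, patients gaining 0.5 or 1 point per week pass the first check 43% or 30% of the time with scores rounded to integers, 50% or 36% unrounded, and 30% or 20% if neither weekly score may exceed the first. The figure depends on choices the article does not fix.
- **That mRS change during the run-in could test the 0.1% assumption.** Second registration requires mRS 3 to 5, so a patient improving from 3 to 2 leaves the treated set. The run-in is shorter than 180 days, and it may fall before day 180 after onset, when recovery may differ.

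**Conclusion.** The concern holds in two parts. First, the run-in cannot exclude the effects of rehabilitation, because rehabilitation continues for 180 (±14) days in a trial without a control group. At full delivery it amounts to 5.9 to 6.9 times the minimum run-in, and less where the run-in is extended. The consequence is material because the primary test turns on a single improver: a true background rate of 1% instead of 0.1% raises the chance of a positive result at n = 10 from 1.0% to 9.6%, and a rate of 5% raises it to 40%. The 1% and 5% are illustrations, since the documents give no observed background rate. Second, the run-in intensity at second registration contradicts the Study Design text and sits badly with the first-registration criterion.

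The finding does not show that the result will be biased by a given amount or that intensity will in fact rise. It shows that a positive primary test would not support an effect specific to the cells.

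**What to change.** 1. Restate the purpose of the run-in in Study Design, and the conclusion to be drawn from the primary test, along these lines: *The run-in is intended to bring patients to a stable level before baseline. Improvement in mRS will be interpreted as change after MSC infusion together with continued rehabilitation; the design does not separate the two.*
2. Reconcile the run-in wording in Study Design, first-registration criterion 4 and second-registration criterion 2. Which intensity applies is for the investigators to decide; the three places should agree.
3. Where delivered rehabilitation minutes are available, tabulate them per patient before and after infusion. The article does not say that they are recorded, so this needs checking first. With 6 to 20 patients, a listing is more useful than a subgroup analysis.
4. Change in mRS between first and second registration may be shown descriptively, but not as a check on the 0.1% assumption.

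The cost is some rewording and one table, with no added visits. The downside is a weaker claim.

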### Sample Size

We will recruit 10 people (minimum: 6; maximum: 20) with a modified Rankin Scale (mRS) grade of 3 to 5. The focus of our trial is to establish safety and potential efficacy. However, it should be noted that if the proportion of cases in which the mRS grade improves by 1 point or more exceeds 10%, the trial will provide significant clinical benefit. To detect a difference by using a *Z*-test with continuity correction, a minimum of 6 people is required. Thus, the target sample size of people with an mRS grade of 3 to 5 was determined to be 10 (minimum: 6; maximum: 10), under the consideration of dropout.

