#### Primary Outcome Measure

The valid target population is patients with an mRS grade of 3 to 5 before MSC infusion. We assume that the proportion of cases without MSC infusion in which the mRS grade improves by 1 point or more will be 0.1%. We will perform a Z-test with continuity correction at 180 (±14) days after MSC infusion.

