### Access to Data

All investigators will have access to the trial data.

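### The Sample Size section gives two different maxima, 20 and 10, and the abstract gives 20; the choice roughly doubles the small false-positive risk and moves power by more than 20 points

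*Protocol article*

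**What the plan says.** The protocol article gives the number of patients in three places.

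- Sample Size, first sentence: "We will recruit 10 people (minimum: 6; maximum: 20) with a modified Rankin Scale (mRS) grade of 3 to 5".
- Sample Size, last sentence: the target "was determined to be 10 (minimum: 6; maximum: 10), under the consideration of dropout".
- Abstract, Methods: "The estimated number of enrolled participants is 6 to 20 patients", in the same mRS range.

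Between the two Sample Size statements, the section says that for the continuity-corrected Z-test "a minimum of 6 people is required". Under Primary Outcome Measure the reference rate is fixed: "We assume that the proportion of cases without MSC infusion in which the mRS grade improves by 1 point or more will be 0.1" per cent.

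Other relevant features are stated elsewhere. The trial is single-arm and open-label (Study Design), registration lasts 5 years (Results), and the primary outcome is read 180 (±14) days after infusion (Primary Outcome). The Access to Data section says "All investigators will have access to the trial data".

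**The concern.** A maximum of 10 and a maximum of 20 cannot both hold for the same population, target and minimum. If 10 is right, the abstract and the opening sentence of Sample Size are wrong. If 20 is right, the conclusion of the sample-size derivation is wrong.

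The conflict is more than a misprint because of where it falls. With so low a reference rate, one improved patient may be enough for significance at any permitted size. The maximum then largely sets the chance that the trial is called positive. A trial with no responder among 10 patients could continue to 20 and still comply with two of the three statements. Registration lasts 5 years against a 180-day outcome, and the data are open, so early results can be known while enrolment continues.

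**Working it through.** **Inputs.** Sizes 6, 10 and 20 (Sample Size, Abstract). Null rate p0 = 0.001 (Primary Outcome Measure). The rate of 10% is the protocol's own benefit threshold (Sample Size). The true rate of 5% is an assumption of this check. The article does not state alpha or sidedness; results are compared with 1.96 (two-sided 5%, one-sided 2.5%).

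**Step 1: the plan's own figure of 6.** Take p1 = 10%, as no other alternative is given, and d = p1 − p0 = 0.099. The usual formula is n = [(z_α√(p0(1−p0)) + z_β√(p1(1−p1)))/d]², with continuity correction n′ = (n/4)[1 + √(1 + 2/(n·d))]². At alpha 0.05, one- or two-sided, this gives 7 at 50% power and 19 at 80% power. Exact power at n = 6 is 1 − 0.9⁶ = 46.9%. Without the stated alpha and power, 6 cannot be reproduced uniquely. Going from 6 to 10 corresponds to 6/(1 − 0.40), that is, a 40% dropout allowance. The section's derivation thus runs from 6 to 10; nothing in it produces 20.

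**Step 2: how many responders are needed.** With one responder, z = (1/n − p0 − 1/(2n)) / √(p0(1−p0)/n).

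- n = 6: 0.08233/0.01290 = 6.38
- n = 10: 0.04900/0.009995 = 4.90
- n = 20: 0.02400/0.007068 = 3.40

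z falls as n grows and is still well above 1.96 at 20. With no responder the test cannot be significant. So success means at least one responder, at every size from 6 to 20.

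**Step 3: chance of a positive result.** P = 1 − (1 − p)ⁿ.

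| True rate p | n = 6 | n = 10 | n = 20 |
|---|---|---|---|
| 0.1% (stated null) | 0.6% | 1.0% | 2.0% |
| 5% (assumed) | 26.5% | 40.1% | 64.2% |
| 10% (benefit threshold) | 46.9% | 65.1% | 87.8% |

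Moving the maximum from 10 to 20 adds 1.0, 24.1 and 22.7 percentage points.

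**Step 4: do repeated looks add to this?** Suppose enrolment continues until the first responder, with maximum N. The trial fails only if all N patients are non-responders, so P = 1 − (1 − p)ᴺ, exactly the fixed-n value. The difference comes from the larger N alone.

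**Step 5: effect on the estimate, extreme case.** Suppose enrolment stops at the first n ≥ 6 with a responder, and otherwise at N, with each result known before the next patient enters. The mean reported proportion is p + Σ p(1−p)ⁿ⁻¹/n, summed over n = 7 to N. The first term is the contribution of stopping at 6. At p = 5%:

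- N = 10: 0.0500 + 0.01645 = 0.06645, or 6.6%
- N = 20: 0.0500 + 0.0330 = 0.0830, or 8.3%

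**The case against.** The strongest reply is that the table in step 3 shows power, not inflation. A rate of 5% is fifty times the stated null, and a trial prespecified at 20 would have the same 64%. That stands.

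A reader might infer that the open range inflates the type I error. The documents do not support this. Under the stated null the probability is 1.0% or 2.0%, below 2.5% even if enrolment follows the results to 20. A type I error above nominal can be obtained by treating 10% as the null and running an exact test after each patient up to 20, but that is not this trial's test. The protocol uses 10% as a benefit threshold and plans a Z-test against 0.1%.

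A reader might also infer that the sponsor intends to stop or extend on results. No interim look, early stop or extension is described, and the access statement does not say that accumulating outcomes will guide recruitment. A closing rule may be in the full protocol or the SAP, neither of which is shown, so its absence from an article is not a finding. Protocol changes also need IRB and PMDA approval (Ethics Approval). That would cover going past a maximum of 10, though not stopping inside the range. The bias in step 5 is an upper case, since two-step registration, cell culture, the rehabilitation plateau and the 180-day wait mean that further patients would usually be under way when a responder appears.

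One might try to reconcile the figures by taking 20 as first registrations and 10 as infused patients. The text does not draw that distinction and attaches the same target and minimum to both.

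None of these replies removes the contradiction between 10 and 20.

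**Conclusion.** The maximum sample size is stated inconsistently in current text, on a figure the trial relies on, and is wrong as written. The choice between 10 and 20 changes the chance of a positive result from 1.0% to 2.0% under the stated null, from 40% to 64% at an assumed true rate of 5%, and from 65% to 88% at 10%. These figures rest on the planned test against 0.1%, under which one responder suffices, and on all counted patients having an outcome.

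The claim stops there: no nominal error rate is exceeded, and result-driven stopping is left open rather than planned. If stopping did follow results in the most extreme way, a true 5% would be reported on average as 6.6% (maximum 10) or 8.3% (maximum 20), because the planned estimate and interval assume a fixed number.

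**What to change.** State one maximum in the abstract and in both sentences of Sample Size. The derivation's own conclusion is 10; any single prespecified number would remove the contradiction, provided the derivation is made to lead to it. Add that enrolment ends at that number or at the calendar end of registration, regardless of observed mRS results, and that the primary test is done once, after the last day-180 visit. If the full protocol or SAP already contains such a rule, a cross-reference is enough.

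The cost is a few sentences in the protocol and SAP, with the approvals that the protocol requires for changes. The sponsor gives up the freedom to extend enrolment after seeing results. The change does not alter the fact that one responder suffices, which follows from the 0.1% reference rate.
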